#### Outcome evaluation

The primary analysis will be completed on an intention-to-treat plan with secondary analysis completed on per-protocol study drug allocation. All analysis will be subject to an $$\alpha$$ level of 0.05 on two-sided testing, and findings will be reported using CONSORT guidelines [53]. Trial results will be disseminated through ClinicalTrials.gov and peer reviewed publication.

The primary outcome will be analyzed using linear mixed-effects model analysis with MWD at 180 days as the outcome variable, a fixed effect for treatment assignment, and covariate adjustment for patient baseline MWD [60, 61]. This approach addresses the study question systematically: For 2 patients with the same pre-trial MWD, one given metformin and one placebo, what is the estimated difference in MWD after 180 days of study drug exposure? The approach, with a covariate adjustment for the baseline measure, is preferred over change scores due to favorable estimation properties and increased statistical power [61]. The model will adjust for baseline covariates with known strong associations to PAD outcomes (age, smoking status, and ABI [8]) to improve precision and increase statistical power [60, 61]. As randomization will be stratified by baseline MWD (MWD < 200 or  $$\ge$$ 200 m) and smoking status, we will test the interaction between these factors and treatment assignment to determine if the treatment effect is different for patients across the baseline MWD stratum.

Secondary outcome analysis will mirror that of the primary outcome for continuous variables. Each of the exploratory secondary outcomes, best summarized as time-to-event (amputations, vascular interventions, MACE, and all-cause mortality), will be reported using Kaplan–Meier analysis, log-rank tests, Cox proportional-hazards, and Fine-Gray models to estimate the difference between treatment groups, controlling for the competing risk of mortality, as appropriate. The MOBILE IC trial is not powered to test for differences in these outcomes but they are included to assess safety, mechanisms of action, allow for future secondary analysis with related studies, as described below, and inform future clinical trials of metformin in PAD and other diseases.

Secondary analysis of outcomes will include per protocol analysis as well as a Bayesian statistical analysis plan.

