## Abstract

**Background:**

Peripheral artery disease (PAD) affects over 230 million people worldwide and is due to systemic atherosclerosis with etiology linked to chronic inflammation, hypertension, and smoking status. PAD is associated with walking impairment and mobility loss as well as a high prevalence of coronary and cerebrovascular disease. Intermittent claudication (IC) is the classic presenting symptom for PAD, although many patients are asymptomatic or have atypical presentations. Few effective medical therapies are available, while surgical and exercise therapies lack durability. Metformin, the most frequently prescribed oral medication for Type 2 diabetes, has salient anti-inflammatory and promitochondrial properties. We hypothesize that metformin will improve function, retard the progression of PAD, and improve systemic inflammation and mitochondrial function in non-diabetic patients with IC.

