**Methods:**

200 non-diabetic Veterans with IC will be randomized 1:1 to 180-day treatment with metformin extended release (1000 mg/day) or placebo to evaluate the effect of metformin on functional status, PAD progression, cardiovascular disease events, and systemic inflammation. The primary outcome is 180-day maximum walking distance on the 6-min walk test (6MWT). Secondary outcomes include additional assessments of functional status (cardiopulmonary exercise testing, grip strength, Walking Impairment Questionnaires), health related quality of life (SF-36, VascuQoL), macro- and micro-vascular assessment of lower extremity blood flow (ankle brachial indices, pulse volume recording, EndoPAT), cardiovascular events (amputations, interventions, major adverse cardiac events, all-cause mortality), and measures of systemic inflammation. All outcomes will be assessed at baseline, 90 and 180 days of study drug exposure, and 180 days following cessation of study drug. We will evaluate the primary outcome with linear mixed-effects model analysis with covariate adjustment for baseline 6MWT, age, baseline ankle brachial indices, and smoking status following an intention to treat protocol.

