### Study aims and outcomes

The MOBILE IC trial aims to establish the effectiveness of metformin on improving overall functional status, PAD progression, and systemic inflammation and cellular respiration in Veterans with PAD and IC. The primary objective is to evaluate the effectiveness of metformin as a pharmacologic treatment for PAD and IC with a Phase III randomized controlled trial. Outcomes are validated and reproducible measures will be used in the evaluation of PAD and IC.

The primary outcome of interest is the maximum walking distance (MWD) on the 6-min walk test (6MWT) [34]. This is a validated measure of functional status in PAD and IC, is highly reproducible, and correlates best with real-life walking capacity [34–36]. Secondary assessments of functional status include distance to claudication pain and rest on the 6MWT, aerobic and anaerobic capacity during cardiopulmonary exercise testing (CPET), Walking Impairment Questionnaire [37], and grip strength. CPET indices include peak oxygen uptake (VO_2_), ratio of minute ventilation (VE) to exhaled carbon dioxide (VCO_2_) or breathing efficiency (VE/VCO_2_), respiratory exchange ratio (VCO_2_/VO_2_), heart rate, and blood pressure [38, 39]. Ventilatory anaerobic threshold (i.e. change from aerobic to anaerobic metabolism, and point of IC onset during CPET are also assessed [38]. CPET measures of symptom-limited (maximal) aerobic and anaerobic capacity in patients with PAD and IC correlate with *systemic* disease severity and outcomes [38, 39]. Functional outcomes will be supported by the general (SF-36) and disease specific (Vascular Quality of Life Questionnaire-6 [VascuQoL-6]) health related quality of life questionnaires.

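### All secondary outcomes are tested at an unadjusted two-sided 0.05, yet the trial aims to establish effectiveness in domains that only secondary or mechanistic measures cover

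*Protocol article*

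**What the plan says.** **Primary outcome.** There is one. The abstract states: "The primary outcome is 180-day maximum walking distance on the 6-min walk test (6MWT"). The power analysis is built on it alone.

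**Error level.** The Outcome evaluation section puts all analyses at an alpha "level of 0.05 on two-sided testing, and findings will be reported using CONSORT guidelines". It then adds: "Secondary outcome analysis will mirror that of the primary outcome for continuous variables". The section gives no gate on the primary result, no order of testing and no division of alpha.

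**Aim.** Study aims and outcomes says that the trial "aims to establish the effectiveness of metformin on improving overall functional status, PAD progression, and systemic inflammation and cellular respiration". The abstract turns the same domains into hypotheses: "We hypothesize that metformin will improve function, retard the progression of PAD, and improve systemic inflammation and mitochondrial function in non-diabetic patients with IC".

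**Qualifications given.** The Outcome evaluation section applies the exploratory label to the event outcomes ("Each of the exploratory secondary outcomes, best summarized as time-to-event") and says that the trial is not powered for them. Study aims and outcomes calls the neutrophil-trap and exosome work exploratory. It presents the inflammatory biomarkers and mitochondrial measures as a means of understanding mechanism. The continuous functional, quality-of-life and vascular outcomes (ABI, PVR, EndoPAT) carry no exploratory label.

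**The concern.** The aim uses a confirmatory verb for several domains, but the primary outcome informs only part of the first, functional status. PAD progression rests on ABI, PVR, EndoPAT and the clinical events. Inflammation rests on seven biomarkers, and cellular respiration on mitochondrial measures supported by exercise-test oxygen uptake. Each continuous measure is tested at the same level as the primary, whatever the primary shows.

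What is at stake is the conclusion after a null or borderline primary. With many secondary tests at 0.05, some nominally significant result is fairly likely by chance. The stated aim then invites it to be reported as effectiveness shown in that domain. The article states both the testing level and the aim, so the mismatch is in its text and is not merely a detail left out.

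**Working it through.** **No figure to reproduce.** The article states a per-test level of 0.05 and no family-wise error rate. The check is what that level implies across the secondary outcomes if metformin has no effect on any of them.

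**Counts, from the article.**
- Abstract, continuous items: cardiopulmonary exercise testing, grip strength, walking questionnaire (3); SF-36, VascuQoL (2); ABI, PVR, EndoPAT (3); inflammation (1). Total k = 9. The four event outcomes are left out because they are labelled exploratory.
- Study aims and outcomes, itemised:
  - two further 6MWT distances, seven exercise-test measures (peak VO2, VE/VCO2, respiratory exchange ratio, heart rate, blood pressure, anaerobic threshold, claudication onset), walking questionnaire, grip strength: 11
  - quality of life, one score each: 2
  - ABI, PVR, reactive hyperemia index, augmentation index: 4
  - inflammatory biomarkers: 7
  - mitochondrial measures: 4
  - total k = 11 + 2 + 4 + 7 + 4 = 28; without the 11 biomarker and mitochondrial measures, k = 17

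**Assumption.** The article gives no correlations between outcomes. I assume a common correlation ρ between test statistics and show the range from 0 to 0.8.

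**Formulas.** With independent tests, P(at least one p < 0.05) = 1 − 0.95^k:
- k = 9: 1 − 0.630 = 0.370
- k = 28: 1 − 0.238 = 0.762

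With common correlation ρ and u standard normal:

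P = 1 − E_u[{Φ((1.96 − √ρ·u)/√(1−ρ)) − Φ((−1.96 − √ρ·u)/√(1−ρ))}^k]

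For false benefit only, code each measure so that benefit is positive and drop the second Φ. Under independence this becomes 1 − 0.975^k.

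**Results by numerical integration.**

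| Set of tests | k | ρ = 0 | ρ = 0.3 | ρ = 0.5 | ρ = 0.8 |
|---|---|---|---|---|---|
| Abstract, continuous items | 9 | 37% | 33% | 27% | 17% |
| Itemised, without biomarkers and mitochondria | 17 | 58% | 49% | 39% | 21% |
| Itemised, all continuous | 28 | 76% | 64% | 49% | 25% |
| Inflammatory biomarkers only | 7 | 30% | 27% | 23% | 15% |
| Vascular measures only | 4 | 19% | 17% | 16% | 11% |
| False benefit only, abstract items | 9 | 20% | 17% | 13% | 8% |
| False benefit only, itemised | 28 | 51% | 34% | 25% | 13% |

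All rows except the last two count either direction and one test per measure at day 180. Tests at day 365, per-protocol analyses and questionnaire subscales would raise the counts.

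**The case against.** **An unseen plan may settle this.** A condensed article commonly leaves hierarchies to the full protocol or SAP, and a per-test level neither claims family-wise control nor rules out an ordering. That stands as a caution: a hierarchy may already exist. It does not remove the point, because the article itself applies 0.05 to all analyses and sets the aim. Any such hierarchy would require that sentence to be qualified.

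**The secondary domains are not put on a level with the primary.** This also stands. The aims section names one primary objective and one primary outcome, and presents quality of life as support for the functional results. The mechanistic framing covers 11 of the 28 measures. That framing makes the aim sentence harder to defend, since the same section proposes to establish effectiveness in the domains those measures represent.

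**Stronger readings.** A reader might infer that a false claim is about as likely as not. The article supports no such single figure. It takes about 28 tests at correlation 0.5, or 13 to 14 independent tests, and the article gives neither a test count nor correlations. It also counts both directions, while the worry is mainly false benefit. A reader might further infer that one significant cytokine in seven would, by rule, prove an anti-inflammatory effect. The article sets a test level and contains no such rule. Finally, dividing these rates by 0.05 to show inflation would compare a family-wise rate with a per-test level.

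**A compulsory fixed sequence across aims is debatable.** Agreed. One early failure would block every later aim, so a sequence should be optional.

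**Conclusion.** The point holds as a mismatch between the stated aim and the stated testing rule. The primary test is sound and keeps its 5% error. In the most favourable case computed (9 measures, correlation 0.8), the chance of some false-positive continuous secondary result is still 17%. With 28 independent measures it is 76%. False benefit alone is about 13% to 25% at correlation 0.5.

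These figures rest on no true effect on any secondary outcome, an assumed common correlation, and my own count of tests from the article. The exact size is therefore uncertain. The conclusion is not: secondary domains tested this way cannot be established at a 5% error rate across the family. This calls for a low-cost improvement in wording and does not threaten the design.

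**What to change.** In the Outcome evaluation section, replace the blanket alpha sentence with wording such as:

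> The primary outcome (180-day MWD, intention-to-treat) is tested at two-sided 0.05. All secondary, mechanistic, day-365, per-protocol and treatment-by-stratum interaction analyses are exploratory and are reported as estimates with 95% confidence intervals, without a claim of effectiveness.

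In Study aims and outcomes, keep *establish* for the primary outcome and use *evaluate* for the other domains.

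If the sponsor wants a confirmatory claim on a secondary aim, it can name a few key secondary outcomes before unblinding and test them in a set order, only after a significant primary. If the full SAP already does this, align the article with it.

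The change needs no extra patients or data and leaves the primary test and its power as they are. The cost is that an isolated secondary p < 0.05 can no longer be presented as established benefit. If the optional sequence is used, a failure early in it closes the later claims.

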#### Randomization, allocation concealment, and blinding

Study participants will be recruited from both in-person and virtual VAPHS vascular surgery clinics. Individuals meeting all inclusion and no exclusion criteria and agree to participate will be randomly assigned 1:1 to 180 days of metformin or placebo treatment (Table 1). The randomization table has been generated by the study statistician and provided to VAPHS Investigational Drug Service (IDS) for study drug allocation. The IDS will maintain the list of allocations for the duration of the study, but has no role in study recruitment, thereby preserving allocation concealment at the point of enrollment. The research staff enrolling participants have no knowledge of allocations. When an eligible participant is enrolled in the study, the VAPHS IDS is informed who then selects the next allocation from the correct sequence. Randomization will be stratified on baseline MWD on the 6MWT as guided by Fontaine Classification (Stage IIA: IC pain at ≥ 200 m; Stage IIB: < 200 m) [45] and smoking status. Within each stratum, variable block sizes (ranging from 2 to 6) are used to further protect allocation concealment. As a placebo-blinded trial, participants and research staff will not know their assignment, but variable block sizes within each stratum provides an additional layer of protection against research staff guessing future allocations. Stratified randomization is employed to maximize statistical power and allow for non-biased subgroup analysis [46].

**Table 1 Tab1:** Inclusion and exclusion criteria

Inclusion criteria: subjects must meet all the following	
	Male and female Veterans > 35 and < 89 years of age
	Symptoms of intermittent claudication
	Diagnosis of PAD as defined by ABI < 0.9 or $$\ge$$ 0.9 with evidence of PAD as documented by pulse volume recordings (within 180 days prior to expected randomization)
	Medically stable, optimal medical therapy ($$>$$ 3 months prior to randomization)
	Maximum Walking Distance (MWD) on the 6-min walk test (6MWT) of ≥ 50 m with onset of pain before or at 400 m without the use of a walker
Exclusion criteria*:* subjects cannot possess any of the following	
General	
	Investigator expects inclusion could cause harm to subject
	Currently taking metformin or have taken metformin (within 180 days of expected randomization date)

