### Statistical analysis plan

#### Power analysis

In accordance with trial design and reporting guidelines, sample size calculations focused on the primary outcome and efficacy of metformin in the treatment of IC [51–53]. The sample size was calculated to provide adequate power to assess clinically meaningful differences in the primary outcome between treatment and control groups. Based on the correlation with an associated decrease in mortality and improvement in health related quality of life, a large meaningful change of MWD is defined as 20–50 m which is the equivalent of a 5–100% change over baseline [54, 55]. Supervised exercise and endovascular intervention trials in PAD found a significant increase in MWD on 6MWT compared to control over 12 to 52 weeks with the effect size $$\pm \hspace{0.17em}$$standard deviation range of 22.2 $$\pm \hspace{0.17em}$$52.1 to 53.5 $$\pm \hspace{0.17em}$$105.0 m [56, 57]. The aforementioned initial Italian studies of non-diabetic patients with IC found a 53% increase in exercise capacity after 180 days of metformin exposure [33].

Assuming a baseline mean MWD of 300 $$\pm \hspace{0.17em}$$100 m in the overall trial population with a mean improvement of 30 $$\pm \hspace{0.17em}$$60 m in the metformin group versus 0 $$\pm \hspace{0.17em}$$60 m in the placebo group, a sample size of 80 patients per group will have 85% power to detect an improvement in MWD at 180 days in response to metformin versus placebo. Stratification of baseline MWD potentially reduces the variation between randomized groups and increases statistical power [46, 58]. The magnitude of power gained cannot be precisely quantified; thus, we did not adjust our sample size estimation for stratification. Therefore, allowing for a conservative 20% dropout rate, consistent with recently completed PAD and VA trials, we will use a total sample size of 200 with 100 per treatment group [14, 59]. Study advertisement and support will be provided to the primary care and cardiology departments within the VAPHS as needed to support enrollment.

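### Effect modification by walking distance is tested only on a 200 m split, which loses roughly half the information if the effect changes linearly with baseline MWD

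*Protocol article*

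**What the plan says.** In the protocol article, the section Outcome evaluation models 180-day MWD with a fixed effect for treatment and "covariate adjustment for patient baseline MWD". It then turns to the randomisation strata ("As randomization will be stratified by baseline MWD (MWD < 200 or" at least 200 m, and smoking status) and says the analysis will test how treatment interacts with them "to determine if the treatment effect is different for patients across the baseline MWD stratum". The interaction is therefore on the two-level stratum. No interaction of treatment with MWD as a continuous measure is stated.

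The section on randomisation gives the purpose of the strata: "Stratified randomization is employed to maximize statistical power and allow for non-biased subgroup analysis". It calls the stratum baseline MWD but takes the 200 m boundary from the Fontaine stages, which it words by the distance at which claudication pain occurs.

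The Power analysis supplies the distribution: "Assuming a baseline mean MWD of 300", with a standard deviation of "100 m in the overall trial population".

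**The concern.** A cut at 200 m lies one standard deviation below the assumed mean, so one of the two groups is small. An interaction test on such an unequal split is imprecise. Replacing a measured distance by above or below a threshold also discards the variation within each group.

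Whether the drug works differently in patients with different walking capacity is a question the article itself poses. It poses it again for the pooled analysis with the companion trial, where baseline MWD is a named subgroup. With the planned test, a difference between strata as large as the whole assumed treatment effect would usually be missed, although the data for a more efficient test are already in the model.

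**Working it through.** **Inputs.** From the Power analysis: baseline MWD 300 ± 100 m; improvement 30 m versus 0 m with SD 60 m in each arm; 80 evaluable per arm; 200 randomised after 20% dropout. From Outcome evaluation: the 200 m cut and two-sided alpha of 0.05. Not in the article: a roughly normal baseline MWD and an effect linear in MWD.

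**The plan's own figure.** The article gives no power for the interaction, only 85% for the primary comparison. SE = 60 × √(2/80) = 9.49 m; 30/9.49 = 3.16; 3.16 − 1.96 = 1.20; power = Φ(1.20) = 88.5% (88.2% by t-test). The stated 85% is a little conservative. This is a separate matter and does not affect the point. The dropout step reproduces: 160/0.8 = 200.

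**Stratum size.** p = Φ((200 − 300)/100) = Φ(−1) = 15.9%. That is about 32 of 200 randomised and 80 × 0.159 = 12.7 completers per arm, against 67.3 in the upper stratum.

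**Planned test.**
- SE = 60 × √(2/12.7 + 2/67.3) = 26.0 m
- Detectable with 80% power: 2.80 × 26.0 = 73 m, or 2.4 times the assumed 30 m effect
- Power for a 30 m difference: Φ(30/26.0 − 1.96) = 21%
- Power for 50 m: just under 50%; for 60 m: about 64%

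**Continuous test of the same contrast.**
- Distance between stratum means: φ(1)/[p(1 − p)] = 0.242/0.1335 = 1.81 SD = 181 m
- SE per 100 m: 2 × 60/√160 = 9.49 m; over 181 m: 9.49 × 1.81 = 17.2 m
- Detectable with 80% power: 2.80 × 17.2 = 48 m
- Power for a 30 m contrast: Φ(30/17.2 − 1.96) = 41%

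**Relative efficiency.** φ(1)²/[p(1 − p)] = 0.439, the same as (17.2/26.0)². So 56% of the information on a linear interaction is lost. In a simulation with 160 patients and a slope of 26.6 m per 100 m, the split had 43% power and the continuous term 79%.

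The 60 m is the SD of improvement. If covariate adjustment leaves a smaller residual SD, both standard errors shrink in the same proportion and the ratio is unchanged.

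**Sensitivity of the share and the loss.**

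| Baseline MWD | Below 200 m | Information lost |
|---|---|---|
| Normal, 300 ± 100 | 15.9% | 56% |
| Same, truncated at the 50 m entry limit | 15.3% | 58% |
| Lognormal, 300 ± 100 | 13.8% | 73% |
| Gamma, 300 ± 100 | 15.3% | 67% |
| Symmetric beta on 50–550 m | 18.1% | 53% |
| Uniform, 300 ± 100 | 21.1% | 50% |
| Left-skewed gamma, 300 ± 100 | 15.5% | 48% |
| Normal, 275 ± 100 | 22.7% | 48% |
| Normal, 250 ± 100 | 30.9% | 42% |

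Even at a mean of 250 m, the stratum SE is 9.49/√(0.309 × 0.691) = 20.5 m, with 2.80 × 20.5 = 57 m detectable. If the effect is flat on each side of 200 m and steps there, the split loses nothing.

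**The case against.** The 200 m cut is not arbitrary. It is the boundary between two recognised Fontaine stages, it is fixed before randomisation, and the blocks balance treatment within it. Testing treatment by a stratification factor is conventional, and whether the effect differs between clinical stages is a slightly different question from whether it varies along the MWD scale. The test is supplementary, and nothing in the article prevents a continuous analysis as well. The article also plans MWD subgroups in pooled data with an expected 412 patients. All of this stands and limits the weight of the point. It supports reporting the strata. It does not make the split the better primary test of effect modification, and pooling does not in itself remove the dichotomy.

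The stratum share is also open to challenge. The strata are named by MWD while the Fontaine stages are worded by pain distance. Pain cannot start beyond the distance walked, so a pain-based stratum would put at least as many patients below 200 m, probably more. The 16% and the loss figures would then not carry over directly.

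A reader might go further and infer three things that the article does not support:
- **That the test cannot detect any plausible interaction, or will be non-significant whatever the truth.** With an SE of 26.0 m, power is just under 50% at 50 m, the top of the range the Power analysis calls a large meaningful change, and 80% at 73 m.
- **That a null result will be reported as no difference between strata.** The article gives no rule for interpreting a non-significant interaction; it says only that reporting follows CONSORT.
- **That the continuous test would be adequately powered.** At 41% for a 30 m contrast, it would still miss such a difference more often than not.

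**Conclusion.** The point holds as one of efficiency in a secondary test. Under the plan's inputs and rough normality, the stratum interaction has low power for a difference the size of the assumed main effect. A continuous linear term would carry 1/0.439 = 2.3 times the information. The size of that gain depends on the shape and mean of baseline MWD and on linearity. The low power of the stratum test depends only on how unequal the split is. The primary model, sample size and alpha are untouched.

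**What to change.** Pre-specify treatment × continuous baseline MWD as the interaction test. Add a spline version as a check on linearity, and show the fitted treatment effect with its confidence interval across the MWD range. Keep the estimates for the two 200 m (Fontaine) strata, with confidence intervals, as supportive description. State that a non-significant interaction will not be read as evidence of a uniform effect. Reconcile the wording of the stratum in the randomisation section, so that it is clear whether MWD or pain distance decides it.

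The cost is one model term and a linearity assumption, which the spline examines. No new data are needed, and randomisation and the primary analysis stay as they are.
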